## Abstract

*Background*: Young children are prone to low levels of physical activity in childcare. This environment, inclusive of equipment, policies, and staff, has been identified as influencing young children’s activity behaviours. To date, no study has examined the feasibility and effectiveness of such policies in Canadian childcare centres, while the provision of physical activity policies in other countries has shown some promise for improving the activity levels of young children. As such, the primary objective of the Childcare PhysicaL ActivitY (PLAY) Policy study is to examine the feasibility of an evidence-based, stakeholder-informed, written physical activity and sedentary time policy for centre-based childcare (i.e., at the institutional level). The secondary objectives are to examine the impact of policy implementation on the physical activity levels and sedentary time of young children, subsequent environmental changes in childcare centres, and childcare providers’ self-efficacy to implement a physical activity policy. This study will examine both policy implementation and individual (behavioural) outcomes. *Methods/Design*: The Childcare PLAY Policy study, a pilot, cluster-randomized controlled trial, involves the random allocation of childcare centres to either the experimental (*n* = 4) or control (*n* = 4) group. Childcare centres in the experimental group will adopt a written physical activity policy for eight weeks (at which time they will be asked to stop enforcing the policy). Physical activity levels and sedentary time in childcare will be assessed via ActiGraph^™^ accelerometers with measurements at baseline (i.e., week 0), mid-intervention (i.e., week 4), immediately post-intervention (i.e., week 9), and at six-month follow-up. Policy implementation and feasibility will be assessed using surveys and interviews with childcare staff. The Environment and Policy Assessment and Observation Self-Report tool will capture potential changes to the childcare setting. Finally, childcare providers’ self-efficacy will be captured via a study-specific questionnaire. A nested evaluation of the impact of policy implementation on young children’s physical activity levels will be completed. A linear mixed effects models will be used to assess intervention effects on the primary and secondary outcomes. Descriptive statistics and thematic analysis will be employed to assess the feasibility of policy implementation. *Discussion*: The Childcare PLAY Policy study aims to address the low levels of physical activity and high sedentary time observed in childcare centres by providing direction to childcare staff via a written set of evidence-informed standards to encourage young children’s activity and reduce sedentary time. The findings of this work will highlight specific aspects of the policy that worked and will inform modifications that may be needed to enhance scalability. Policy-based approaches to increasing physical activity affordances in childcare may inform future regulations and programming within this environment.

## 1. Background

Young children’s regular participation in physical activity positively impacts many aspects of health, including the maintenance of healthy body weight [1], cognitive development, and psychosocial and cardiometabolic health [2]. The recently released Canadian 24-Hour Movement Guidelines for the Early Years (0–4 years) provides recommendations regarding the appropriate amount and intensity of daily physical activity and sedentary time for young children [3]. Specifically, from age one, children are recommended to engage in 180 min/day of any intensity physical activity, including some moderate-to-vigorous physical activity (MVPA) [3]. Higher-intensity physical activity, in the form of energetic play, offers additional health benefits, and children three years and older should also engage in at least 60 min/day of MVPA [2,3]. Additionally, screen time should be restricted to no more than 60 min per day [3]. These new guidelines provide a target for parents and are especially important for childcare providers to consider, as more than half (60%) [4] of Canadian children under the age of six spend most of their waking hours enrolled in childcare services. Low levels of energetic physical activity have been reported in this setting (i.e., 1.5 min/h or approximately 12 min of MVPA during childcare hours) [5]; therefore, childcare-based physical activity interventions are necessary to ensure that children in this type of care are afforded sufficient opportunities to meet these guidelines.

Time spent in childcare is oftentimes sedentary [5,6,7,8,9]. Specifically, during childcare hours, Tucker and colleagues [9] noted that preschool-age children spend approximately 33 min/hour in sedentary pursuits, while Erinosho and colleagues reported 3.4 h/day sedentary among this population [7]. Additionally, childcare providers—the individuals responsible for the day-to-day care and programming within these centres—have noted low levels of self-efficacy for engaging children in physical activity [10], and the childcare environment, inclusive of portable play equipment and sedentary affordances, has been noted to influence physical activity opportunities and sedentary pursuits in these centres [5,9]. This is problematic as sedentary behaviours have been shown to negatively relate to motor/cognitive development, psychosocial health, and are linked to indicators of adiposity [11]. While some sedentary behaviours, such as reading, serve important developmental roles for young children, screen time has been noted as particularly detrimental among this cohort [11,12]. Many childcare centres have computers, tablets, and/or televisions available for children to use, and Vanderloo (2014) reported screen time use ranging from 0.1 to 1.3 hours per day in these facilities [12]. Replacing screen-based activities with physical activity affordances may support improved activity behaviours among young children in these settings.

A few studies, to date, have noted higher rates of physical activity participation among children in centres where an activity-specific or screen-viewing policy was in place [13,14,15,16,17]. However, as McWilliams and colleagues found in North Carolina [17], less than 60% of childcare centres had adopted a formal, written physical activity policy. Some of those policies that are in place included “vague statements such as ‘go outside daily, weather permitting’” [18]. Moreover, a number of researchers have noted the need for policies that offer clear guidance for childcare centres, along with specific methods for implementing the physical activity recommendations and tools for measuring the effectiveness of the strategy as well [6,19,20]. Tandon and colleagues further suggested that childcare physical activity policies should focus on outdoor play and adult-led physical activity, given their association with preschoolers’ activity levels [21], and Staiano et al. suggested limiting screen time and ensuring computer usage is for educational purposes only [16].

To gauge the current climate regarding childcare physical activity and screen time policies in Canada, our team recently examined the frequency of institutional-level policies and reviewed provincial/territorial regulations regarding physical activity and screen time [22,23]. At the individual childcare level, directors reported limited physical activity standards, and none explicitly defined a compulsory duration or intensity [22]. Similarly, of the 13 provinces and territories, only three referenced physical activity in their regulations, and of these, only two provide a time requirement for engaging children in physical activity [23]. Additionally, very few childcare centres noted having screen-based policies in place [22], and 92% of provincial/territorial regulations across the country have no stipulations specific to screen time in these settings [23]. Researchers have highlighted the need for more targeted research examining the impact of childcare policy changes on physical activity levels and sedentary time [24]. In Alberta and British Columbia, advances with respect to childcare accreditation standards have been made; specifically, in Alberta, accredited childcare centres are required to provide diverse daily offerings of physical activity, with childcare providers acting as role models for these activities [25]. A quasi-experimental evaluation of these accreditation standards supports the adoption of more specific guidelines to improve children’s physical activity levels and reduce sedentary time during care [26]. However, an examination of the effectiveness of an institutional childcare policy intervention outlining specific recommendations for physical activity among Canadian children has not yet been conducted.

The primary aim of the eight-week Childcare PLAY Policy study is to evaluate the feasibility of an evidence-based, stakeholder-informed, written physical activity and sedentary time policy in childcare centres. For the purpose of this study, feasible refers to the intervention being implemented as intended and well received by childcare providers. Specific objectives include determining whether the policy was effective at: (i) increasing young children’s (i.e., toddlers and preschoolers, age 18 months–4 years) physical activity (i.e., MVPA and total physical activity (TPA)); (ii) reducing young children’s sedentary time; (iii) producing a feasible and appropriate policy for use in the childcare setting; (iv) increasing childcare providers’ self-efficacy for facilitating young children’s physical activity during childcare; and (v) producing environmental changes in support of physical activity in childcare. Because the implementation of a policy may influence other aspects of the childcare, an environmental assessment will also be conducted. This pilot study will evaluate the feasibility and effectiveness of policy implementation within individual childcare centres, and it will afford the opportunity to modify the policy prior to examining its effectiveness in a larger, more diverse sample.

### Hypothesis

It is hypothesized that the physical activity and sedentary time policy will be viewed as feasible to implement. Additionally, it is anticipated that young children who attend a centre implementing the physical activity policy (i.e., experimental group) will display increased rates of TPA, MVPA, and reduced sedentary time from baseline to post-intervention, with no change observed for children at centres assigned to the control group. While activity levels are expected to decrease at follow-up, when providers are asked to stop enforcing the policy, it is believed that activity levels at this time point will still be higher than those recorded at baseline. For childcare providers from the experimental group, we expect an increase in self-efficacy implementing physical activity in childcare after adopting the policy and expect additional supportive changes in the childcare environment as a result of the policy implementation.

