### 2.5. Participants

The project coordinator will invite all toddlers (18 months–2.4 years) and preschoolers (2.5 years–4 years) to participate, and those whose parents/guardians provide written consent will be eligible to participate in the study. Childcare providers and directors from randomly selected childcare centres will also be invited to participate. Participants will receive a small token of appreciation as thanks for their time. See Table 1 for complete inclusion/exclusion criteria for the Childcare PLAY Policy study.

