### 2.6. Development and Implementation of the Childcare PLAY Policy

To promote policy engagement, buy-in, and suitability, the policy was developed by our research team in collaboration with an advisory committee that included childcare organizations and centre administrators, childcare providers, municipal childcare stakeholders, and a policy expert. The policy was created following a review of relevant literature on the importance of outdoor play [32], unstructured activity [29,33], and informed by the Canadian 24-Hour Movement Guidelines for the Early Years (0–4 years; [3]). The current version of the policy includes eight statements that are designed to provide specific recommendations for time in energetic play (i.e., minimum of 40 min/day), outdoor time (i.e., 120 min/day), and suggests short (i.e., 15–30 min), frequent (i.e., 3–4 times/day) outdoor periods during childcare hours. It requires that children be exposed to a variety of indoor and outdoor physical activities to promote physical literacy and recommends appropriate role modelling of screen-based technology, with no screen time permitted for children during childcare hours. Sustained sedentary time is recommended to be disrupted and replaced with physical activity. See Appendix A for the Childcare PLAY policy.

Experimental Condition. For eight weeks, childcare providers in the experimental centres will be asked to implement the written policy that outlines optimal physical activity daily affordances and sedentary time recommendations during childcare. Prior to the eight-week intervention period, childcare providers will participate in a training session, led by the project coordinator. The session will last approximately an hour in length, which will detail the characteristics of the study design, review the policy, its implementation, and study tools (e.g., accelerometer logs).

Control Condition. Childcare centres randomly assigned to the control group will be asked to continue their typical daily curriculum for the duration of the eight-week intervention and follow-up period. Upon completion of the study, all centres allocated to this group may opt to receive a copy of the written physical activity policy and the training regarding its implementation.

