### 2.8. Analysis

All data will be entered, verified, and stored in our lab. Baseline characteristics of the children and the childcare centres will be summarized descriptively; participant characteristics for those who complete the study and those who drop out will be explored. All statistical analyses will be performed in R [31], using the lme4 [40] and lmerTest packages [41].

Implementation Log. Frequencies and percentage scores will be calculated to reflect adherence to policy statements and reasons that compliance was not attained will be reported descriptively.

Program Evaluation Survey and Interviews. Means and standard deviations of survey item ratings will be provided. Responses to open-ended program evaluation survey and interview questions will be analyzed using thematic content analysis [42] using QSR NVivo.

Physical Activity. Children’s physical activity data will be analyzed using a series of linear mixed effects models for each of the three outcome variables (i.e., TPA, MVPA, and sedentary time). Group (experimental versus control) and time (baseline, mid-intervention, post-intervention, and six-months post-intervention) will be modelled as a fixed effect, and will be evaluated using *t*-tests, with a Satterthwaite approximation determining degrees of freedom. Descriptive survey data will be analyzed using frequencies, *t*-tests, and chi-square tests.

Childcare Providers’ Self-Efficacy. Descriptive statistics will be reported to indicate changes in childcare providers’ self-efficacy specific to implementing physical activity in childcare. Classical test theory will be used to assess internal consistency of the scales, exploratory factor analysis will be used to assess the factorial validity of the measured constructs, and item response theory will be used to explore the item and scale characteristics of the measurements used to assess the two polytomous constructs in this study (i.e., task and barrier self-efficacy). Factor analysis and classical test theory analyses will be undertaken within the psych package [43] and the ltm package [44] will be used for the item response theory analyses.

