## Figures and Tables

**Table 1 ijerph-16-04400-t001:** Inclusion and exclusion criteria for the Childcare PLAY Policy study.

Participant	Inclusion Criteria	Exclusion Criteria
Childcare Centres	Centre-based facility in London, Canada At least one toddler or preschool classroom Childcare providers willing to participate ≥8 children who received parental consent English-speaking centre Does not currently have an institutional-level PA policy	Home-based childcare or after-school care only Not located in London, Canada or surrounding area Do not have a toddler or preschool-age classroom Childcare providers not willing to participate <8 children with parental consent Not an English-speaking facility Already has an established institutional-level PA policy
Childcare Providers	Full-time childcare provider in a toddler/preschool classroom Speaks and writes English	Not full-time Not a childcare provider in a toddler/preschool classroom Does not speak/write in English
Toddler/ Preschool Participants	Enrolled at a participating childcare centre 18 months–4 years Expected to remain at centre for next eight months Enrolled in a toddler/preschool classroom Parent/guardian speaks and understands English Has parental/guardian consent	Not enrolled at a participating childcare centre Not 18 months–4 years Not expected to remain in care for next eight months Not enrolled in a toddler/preschool classroom Parent/guardian does not read/write in English No parental/guardian consent

*Note.* PA = physical activity.

**Table 2 ijerph-16-04400-t002:** Outcome assessments for the Childcare PLAY Policy study.

Participant/Tool		Control Condition				Experimental Condition			
		Baseline (week 0)	Mid-Int (week 4)	Post-Int (week 9)	6M	Baseline (week 0)	Mid-Int (week 4)	Post-Int (week 9)	6M
Toddlers/ Preschoolers	Parent/Guardian Demographic Q	x				x			
	Physical Activity/ Sedentary Time (ActiGraph™ data)	x	x	x	x	x	x	x	x
	Anthropometrics	x				x			
Childcare Providers	Demographic Q	x				x			
	Policy Adherence Log (week 1–8) *		x				x		
	Program Evaluation Survey							x	
	Interview							x	
	EPAO-SR General	x	x	x	x	x	x	x	x
	EPAO-SR Today	x	x	x	x	x	x	x	x
	Self-Efficacy Q	x	x	x	x	x	x	x	x
Directors	Director General EPAO-SR	x				x			

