## Appendix A. Childcare PLAY Policy

Childcare programs encourage all children to engage in physical activity frequently throughout the day, with a focus on outdoor energetic free play and deliberate interruption of sustained periods of sedentary behaviour.

Directed by the Canadian 24-Hour Movement Guidelines for the Early Years (0–4 years)*, childcare programs are expected to:

1. Encourage children to engage in higher intensity energetic play (i.e., activities that induce sweating and heavy breathing) often throughout the day with a goal of accumulating a minimum of 40 min each day. More is better.
2. Expose children to a variety of indoor and outdoor physical activities, including both child-directed and teacher-facilitated active play daily.
3. Outdoor time is offered for a minimum of 120 min each day, unless extreme weather (i.e., heat or cold alert) prevents it. When extreme weather occurs, the opportunity exists for children to engage in active play indoors.
4. Short, frequent outdoor sessions are most conducive to higher intensity physical activity among children; therefore, short bouts (e.g., 15–30 min) of outdoor time are recommended often (e.g., 3–4 times a day).
5. Unstructured (i.e., child-directed) free play is predominant during outdoor time. When activity levels decline, childcare practitioners encourage continued energetic play through structured activity, participation alongside children, and use of verbal prompts.
6. Encourage children to develop physical literacy by practicing fundamental movement skills often throughout the day (e.g., running, skipping, hopping, or jumping).
7. The appropriate use of screen-based technology is role modelled by childcare practitioners by avoiding it when children are present. Screen-based technology is not offered to children under 2 and is not recommended during childcare hours.
8. Programming is designed to break up sustained sedentary time using indoor movement-based activities.

* These guidelines recommend that children over 1 year of age engage in 180 min of physical activity at any intensity each day, and by age 3, at least 60 min of this time is spent in higher intensity physical activity, known as energetic or active play.

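### The six-month maintenance hypothesis names only baseline as its comparator, so ageing or seasonal drift shared by both arms could support or contradict it when the policy has no lasting effect

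*Protocol article*

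**What the plan says.** The Hypothesis section makes two predictions about children's activity.

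- **Baseline to post-intervention.** Children in experimental centres are expected to improve on total physical activity (TPA), moderate-to-vigorous physical activity (MVPA) and sedentary time, "with no change observed for children at centres assigned to the control group".
- **Six months.** Levels are expected to fall once providers stop enforcing the policy, but "it is believed that activity levels at this time point will still be higher than those recorded at baseline". Control children are not mentioned here.

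Section 2.8 (Physical Activity) plans linear mixed models for TPA, MVPA and sedentary time. Group is a fixed effect, and "time (baseline, mid-intervention, post-intervention, and six-months post-intervention) will be modelled as a fixed effect". No group-by-time term or six-month contrast between arms is named.

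The control data exist. Section 2.6 says that control centres "will be asked to continue their typical daily curriculum for the duration of the eight-week intervention and follow-up period", and Table 2 schedules accelerometry in both arms at all four waves.

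On timing, post-intervention is week 9 and the last wave is "six-months post-intervention". Table 1 requires of children: "Expected to remain at centre for next eight months". On weather, Appendix A states: "Outdoor time is offered for a minimum of 120 min each day, unless extreme weather (i.e., heat or cold alert) prevents it".

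**The concern.** A comparison of follow-up with baseline inside the experimental arm measures the residual policy effect plus whatever else changed over the interval. Two other changes are foreseeable from the article itself.

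- **Season.** An interval of about eight months cannot return to the same time of year, and outdoor time, a central part of the policy, depends on weather. Section 2.7 also lists weather among the reasons for non-adherence.
- **Ageing.** Eight months is a large step for children aged 18 months to 4 years, and some toddlers will have moved into the preschool age band.

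Both can occur in control centres as well. A favourable shift could be read as maintenance of the policy's effect, and an unfavourable one as its loss. The discussion says the findings may guide institutional policies and provincial standards, so whether an effect persists matters. The randomised comparison that would separate policy from drift is available, but the hypothesis does not call on it.

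**Working it through.** **1. What each prediction compares.** The short-term prediction has a control reference, but that reference is attached to the period from baseline to post-intervention. It does not extend to six months. The six-month prediction has baseline alone.

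**2. Interval.** Week 9 plus six months (26 weeks) is 35 weeks, about eight months. This agrees with the eight-month stay criterion in Table 1. A toddler aged 22 months at baseline is 22 + 8 = 30 months (2.5 years) at follow-up, the lower bound of the preschool band in section 2.5.

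**3. Illustration.** The article has no figure to reproduce on this point, so the effect of drift is shown under stated inputs.

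- From the article: 4 centres per arm; total variance split by an intra-cluster coefficient of 0.05; 175 children after the design effect, so 175/8 = 21.9, taken as 22 per centre.
- Assumed: half of the intra-cluster coefficient varies by wave (variance 0.025 per wave); within-child correlation ρ of 0.3 to 0.7; no policy effect at six months; the same drift d, in SD units, in both arms.

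Variance of one centre's mean change: V = 2 × 0.025 + 2 × 0.95 × (1 − ρ)/22.

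- ρ = 0.3: 0.050 + 0.0605 = 0.1105
- ρ = 0.7: 0.050 + 0.0259 = 0.0759

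Standard error of the experimental-arm mean change, √(V/4): 0.166 and 0.138.

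Probability that the experimental mean exceeds baseline, Φ(d/SE), and probability that it does so significantly (two-sided 5% t-test on four centre means, 3 df, from the noncentral t with noncentrality d/SE):

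| Drift d | Mean above baseline | Significantly above | Significantly below |
|---|---|---|---|
| −0.2 SD | 7–11% | under 1% | 14–18% |
| 0 | 50% | 2.5% | 2.5% |
| +0.2 SD | 89–93% | 14–18% | under 1% |

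For +0.2 SD: 0.2/0.166 = 1.20 gives 89% and 14%; 0.2/0.138 = 1.45 gives 93% and 18%.

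**4. The alternative contrast.** In the between-arm difference in change, d cancels. A simulation of centre-level change (40,000 runs per setting, 6 df, ρ = 0.5, intra-cluster coefficient of change 0.05) gave two-sided rejection of 4.7–5.1% and rejection in favour of the policy of 2.4–2.5%, for every drift examined from −0.4 to +0.4 SD.

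**5. Price in precision.** The standard error of the difference is √(V/2): 0.235 (ρ = 0.3) and 0.195 (ρ = 0.7), which is √2 times the within-arm value. With 6 df (t = 2.447) the 95% confidence interval is about ±0.48 to ±0.58 SD.

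**The case against.** The strongest reply is that the six-month sentence is a belief about a trajectory and not a decision rule. The trial is a pilot whose primary aim is feasibility. Section 2.8 puts group and all four waves in mixed models, and the control arm is measured at six months. A group-by-time term, which a fuller plan may contain, would deliver the between-arm estimate.

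Much of this stands. A reader might infer that the article sets being above baseline as a success criterion, or that the control arm is left out of the analysis. It does neither: no threshold or within-arm six-month test is stated, and control children enter the models. A reader might also infer that the expected absence of change in control will be accepted on a non-significant test, or that it serves as the six-month reference. No such test appears, and the clause covers only baseline to post-intervention. Nor does the article show that drift will occur. It gives no calendar dates and no seasonal or ageing effect, so the direction of any distortion is unknown.

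The wording of the hypothesis remains a problem. A group-by-time contrast would supply the right estimate, but the prediction as written would still be judged against baseline, and section 2.8 names no six-month contrast to set beside it.

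**Conclusion.** The concern holds as a fault in how one secondary hypothesis is framed. The six-month expectation can be met or missed through drift common to both arms, and neither the Hypothesis section nor section 2.8 directs the reader to the comparison with control.

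The size is conditional. A mean simply above baseline is easily produced by a modest shared rise, whereas a significant rise under a centre-level test is much less frequent, though well above the nominal 2.5% in that direction. These figures rest on assumed drift, correlation and wave-to-wave centre variation, none of which the article gives. The structural point, that shared drift moves the within-arm comparison and cancels from the between-arm one, does not depend on them.

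The change is worth making but does not touch the primary feasibility aim.

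**What to change.** Restate the six-month hypothesis: the change from baseline to six months is greater in experimental than in control centres for TPA and MVPA, with a greater reduction in sedentary time.

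In section 2.8, name the estimate as the group-by-time contrast at six months from the mixed model, reported with a 95% confidence interval. State that within-arm changes from baseline, including those in the control arm, are descriptive and are not evidence of a policy effect.

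The cost is one sentence and one model contrast. No new data are needed, because both arms already have accelerometry at six months. The estimate will be less precise than the within-arm comparison, and with eight centres the interval will be wide. The report should say so and not fall back on the comparison with baseline.
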